## Abstract

**Background:**

Dysphagia can lead to serious complications such as aspiration and aspiration pneumonia, timely and effective rehabilitation training can improve the swallowing function of patients. However, the conventional rehabilitation training methods used in clinical settings have shortcomings such as poor adherence of patients. We present the study design of a randomized controlled trial that evaluated whether video-game based swallowing rehabilitation training can effectively improve swallowing in patients with dysphagia and whether it has additional benefits compared with conventional training methods to improve swallowing function and training compliance among patients with dysphagia.

**Methods:**

A randomized controlled trial with 4 weeks of intervention and 4 weeks of follow-up will be conducted in a rehabilitation center in Beijing, China. We will enroll 78 patients aged 18–80 years with dysphagia. Participants will be randomly assigned to the experimental group (video-game based swallowing function training) and the control group (conventional swallowing function training). All participants will receive 30 min of training per day, 5 times per week, for a total of 4 weeks. The primary outcome is swallowing function. Secondary outcomes include patients' quality of life, training compliance, and training satisfaction. Outcomes are assessed at baseline (pre-treatment), 4 weeks of treatment (post-treatment), and 8 weeks (follow-up), and the assessor is not aware of the participants’ grouping.

**Discussion:**

The protocol describes a new rehabilitation training method for dysphagia, which involves participant eligibility recruitment, recruitment strategies, and data analysis plan. The results of the study will inform the rehabilitation training and clinical care management of swallowing function in patients with dysphagia.

**Trial registration:**

ClinicalTrials.gov, NCT05978700. Registered on 28 July 2023.

## Administrative information

Note: the numbers in curly brackets in this protocol refer to SPIRIT checklist item numbers. The order of the items has been modified to group similar items (see http://www.equator-network.org/reporting-guidelines/spirit-2013-statement-defining-standard-protocol-items-for-clinical-trials/).

## Introduction

### Background and rationale {6a}

Dysphagia is a clinical phenomenon in which the jaw, lips, tongue, soft palate, pharynx, esophagus, and other organs are structurally and/or functionally impaired, preventing the safe and effective delivery of food from the mouth into the stomach [1]. Decreased muscle mass, reduced salivary secretion, and neurological disorders can lead to patients suffering from dysphagia [2]. A global survey reported that 26.2% of older adults, 8.1%-80% of stroke patients, and 11%-81% of Parkinson's patients had dysphagia [3]. Patients have increased complications such as aspiration, aspiration pneumonia, malnutrition, and psychological and social interaction disorders due to dysphagia, which leads to reduced immune response, prolonged patient length of stay in hospitals, increased patient mortality, and hospitalization costs [4].

Functional assessment and timely personalized swallowing training for patients with dysphagia could help improve the coordination of swallowing-related muscles, stimulate the central nervous system, expand the cortical sensory range, and promote the restoration and reconstruction of the swallowing reflex arc, which could effectively improve the swallowing level of patients [5]. However, the existing swallowing training was recently limited by space, the training mode was "one-to-one", and the training process was tedious [6–8]. Park et al. [9] used effortful swallowing training to train the muscles associated with swallowing during the oropharyngeal phase in patients with dysphagia. During the training, the therapist confirmed each patient's completion of an effortful swallow by visual observation and palpation [9]. As the number of patients with dysphagia increases, the "one-on-one" training model will eventually fail to meet the needs of the patients. Simultaneously, the boring and repetitive training leads to low patient compliance and adherence. Intermittent theta burst stimulation (iTBS) and repetitive transcranial magnetic stimulation (rTMS) require the assistance of professional staff and professional rehabilitation training equipment. The existing swallowing training equipments are mostly developed by professional staff, and rehabilitation training activities need to be carried out during hospitalization or in rehabilitation hospitals, making it difficult to achieve remote guidance and intelligence for swallowing function training, which makes patients suffer from untimely training and inappropriate rehabilitation [10, 11].

With the advent of the information technology age, more and more researchers are using video-game to help patients with their rehabilitation training. The researcher applies game thinking to the rehabilitation training environment, screens reasonable gamification intentions for training, creates a world that fits the patient, provides scenarios suitable for the experience of the patient, and enables the patient to engage in a variety of intuitive and natural real-time perceptual interactions such as visual, auditory, and tactile, thus making the rehabilitation process enjoyable and participatory [12, 13].

Video-game was currently rarely used for swallowing training in stroke patients, but mostly for physical and cognitive rehabilitation in stroke patients, and were proven to be effective [14, 15]. Park et al. (2019) designed a game-based chin tuck against resistance exercise to assist in rehabilitating patients with post-stroke dysphagia and found that patients had significantly higher training compliance and motivation scores, significantly lower exercise stamina, and muscle fatigue than the conventional training group [16]. However, Park et al. (2019) only performed the Chin tuck against resistance exercise, which did not include the entire swallowing training process needed for swallowing rehabilitation. Li et al. (2016) used a game-based biofeedback treatment that required patients to complete the training by swallowing hard and wearing a neck accelerometer that sensed the patient's swallowing threshold to enable interaction [17]. However, this study used acceleration curves to provide results on feedback and required lengthy training for medical staff to use. At this stage, there is still a lack of a video-game that are fully-trained and user-friendly for people with dysphagia, and a lack of high-quality, large sample size trials to verify the effectiveness of using video games for rehabilitation.

## Objectives {7}

This study aimed to investigate the effect of video-game on swallowing function in patients with dysphagia through a randomized controlled trial. It is hypothesized that video-game based intervention will improve swallowing function better in patients with dysphagia compared to conventional dysphagia training.

## Trial design {8}

This study is a single-center, single-blind, parallel randomized controlled trial (RCT) with a 4-week intervention and a 4-week follow-up. All phases are conducted according to the SPIRT reporting guidelines [18]. Treatments received will be randomly generated by R software in 1:1 numbers, randomly assigned by a postgraduate student not involved in the assessment and intervention, and placed in opaque closed envelopes. The intervention program will be based on the protocol of this study.

## Methods: participants, interventions and outcomes

### Study setting {9}

The study will be conducted at a rehabilitation center in Beijing, China. Ethical approval for the study has been obtained from the Institutional Review Board of the hospital (Approval No. LS20230720-1) and the study will be conducted with the consent of the hospital and department heads. Informed consent will be obtained from all participants before allocation.

### Eligibility criteria {10}

The inclusion criteria were: (1) diagnosis of dysphagia according to the Toronto Bedside Swallowing Screening Test (TOR‐BSST); (2) age between 18 and 80 years; (3) no significant cognitive impairment, able to execute instructions correctly, and with Mini-Mental State Examination (MMSE) score ≥ 24; (4) be able to use a computer screen with or without the assistance of others; (5) be able to understand and follow instructions; (6) life expectancy estimated by healthcare providers to be ≥ 12 months; and (7) informed consent to the study can be given by signing an informed consent form.

The exclusion criteria were: (1) dysphagia caused by structural lesions (eg, radiotherapy, previous extensive surgery of the head and neck region such as laryngectomy and cordectomy); (2) combined with serious heart, lung, liver, kidney diseases, and hematological disorders; (3) limb deficiency or paralysis, blindness in both eyes, severe visual impairments; (4) motion sickness or vestibular dysfunction; (5) history of epilepsy, malignancy or other neurological diseases; or (6) pregnancy or breastfeeding. Some of the exclusion criteria depended on the video-game device or were precautions designed to not harm participants after using video-game technology. Because of the need to use video games, there is concern that people over the age of 80 will not be able to use computers or view electronic screens, thus limiting participants under the age of 80.

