## Discussion

Swallowing training combined with video games may be a more feasible and effective intervention strategy than using usual care alone to improve swallowing function in patients with dysphagia. However, there is no evidence for the role of video-game based swallowing function training. Therefore, this study aims to provide new insights into whether video-game based swallowing function training can be an effective way to enhance swallowing function in patients with dysphagia. This will be the first known longitudinal study to combine a complete swallowing training program with video-game.

Swallowing movements can be understood as nutritional intake and airway blocking movements. In healthy individuals, the food bolus ingested through the mouth is transported through the esophagus to the stomach [34]. There are four consecutive coordinated phases of swallowing: the oral preparation phase, the oral propulsion phase, the pharyngeal phase, and the esophageal phase. The peripheral muscles involved in swallowing movements include the masticatory muscles, facial muscles, suprahyoid muscles, soft palate muscles, pharyngeal muscles, infrahyoid muscles, and intrinsic lingual muscles [35]. In patients with neurological disorders, central nervous system disorders lead to dysfunction and incoordination of the oropharyngeal muscles, and thus patients are likely to have dysphagia [36]. Also, advanced age or weakness of the muscles of the face, palate, and pharynx may increase the odds in developing dysphagia among patients. Therefore, appropriate muscle rehabilitation is a common and effective way to improve the swallowing function of patients.

Video games have deep potential for patient rehabilitation, such as reducing neuromotor impairment [37], improving cognition and attention [38], reducing anxiety and depressive symptoms [39], or managing chronic conditions [40]. Gamification is a useful strategy to achieve effective completion of rehabilitation by combining it with certain therapeutic interventions [41], such as muscle training, and by inspiring patients with points or rewards to increase their participation and motivation. Some serious games or video games for the education of patients with dysphagia have shown positive results [42]. However, to our knowledge, there are no trials that have studied the evaluation of the effectiveness of video-game for rehabilitation in patients with dysphagia for motor purposes.

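### Exclusion 5, read literally, bars anyone with a neurological history, including stroke and Parkinson's disease, which conflicts with a rationale that rests in substantial part on neurogenic dysphagia

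*Protocol article*

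**What the plan says.** All references are to the protocol article.

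**Eligibility criteria {10}.** Entry requires a "diagnosis of dysphagia according to the Toronto Bedside Swallowing Screening Test"; no inclusion criterion names a cause. Three exclusions bear on cause or neurological status:
- Exclusion 1: "dysphagia caused by structural lesions (eg, radiotherapy, previous extensive surgery of the head and neck region such as laryngectomy and cordectomy").
- Exclusion 3: "limb deficiency or paralysis, blindness in both eyes, severe visual impairments".
- Exclusion 5: "history of epilepsy, malignancy or other neurological diseases".

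The section adds that some exclusions reflect the gaming device or protect participants, without saying which.

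**Background and rationale {6a}.** On causes: "Decreased muscle mass, reduced salivary secretion, and neurological disorders can lead to patients suffering from dysphagia". On burden: "26.2% of older adults, 8.1%-80% of stroke patients, and 11%-81% of Parkinson's patients had dysphagia". On the gap: "Video-game was currently rarely used for swallowing training in stroke patients". The section then builds on an earlier game-based exercise study in post-stroke dysphagia.

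**Discussion.** On mechanism: "In patients with neurological disorders, central nervous system disorders lead to dysfunction and incoordination of the oropharyngeal muscles". The next sentence adds advanced age and weakness of the facial, palatal and pharyngeal muscles.

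**Objectives {7}** and the closing paragraph of the Discussion refer to patients with dysphagia, with no restriction by cause.

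**The concern.** A trial's eligibility rules fix the population to which every result applies, and no later analysis can repair them. Here the rule and the rationale point to different patients. The background motivates the trial partly by stroke and Parkinson's disease, and exclusion 5 as worded turns both away.

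The harm depends on how the criterion is applied:
- **Literally.** The trial would enrol only people whose dysphagia is neither structural nor accompanied by a neurological history. Its result would not answer the question about stroke patients raised in the background, and a conclusion for dysphagia patients at large would reach beyond those studied.
- **Loosely.** Each screener would decide which neurological patients count. The enrolled population would then be undefined, and another team could not reproduce it.

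**Working it through.** No sample-size or power figure bears on this point, so the check sets the eligibility text against the groups named in the rationale.

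**Step 1: apply the exclusions, as written, to each group whose prevalence of dysphagia is quoted.**

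| Group | Prevalence quoted | Exclusion 1 (structural) | Exclusion 3 (paralysis) | Exclusion 5 (neurological history) | Outcome |
|---|---|---|---|---|---|
| Older adults without neurological history | 26.2% | Not caught by age alone | Not caught by age alone | Not caught | Can enter, up to age 80 |
| Stroke | 8.1% to 80% | Not caught | Caught only if paralysed | Caught | Excluded |
| Parkinson's disease | 11% to 81% | Not caught | Not caught as such | Caught | Excluded |

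Exclusion 5 is sufficient on its own for both neurological groups. Exclusion 3 adds little: the word paralysis follows limb deficiency and, read as limb paralysis, removes some stroke patients only. Exclusion 1 removes neither group but narrows what is left.

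**Step 2: test whether the wording contains an exception.** The word 'other' needs something to refer back to. Within exclusion 5, the neurological disease just listed is epilepsy, so 'other' most naturally means other than epilepsy. For it to mean other than the cause of the dysphagia, a cause would have to be named earlier, and no inclusion criterion names one. The criterion also turns on history: a patient whose dysphagia follows a stroke has a history of stroke.

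**Step 3: compare with the rationale.**
- Burden: two of the three quoted groups are neurological.
- Gap: the background says video games have rarely been used for swallowing training in stroke patients. Its closing statement of the gap is broader and refers to people with dysphagia.
- Mechanism: the Discussion gives central nervous system dysfunction first, then age and muscle weakness.

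The justification is therefore mixed, with a substantial neurogenic part that the literal criterion removes.

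**Step 4: look for an acknowledgement.** The four limitations listed in the Discussion cover computer access, blinding, the lack of videofluoroscopy and questionnaire bias. None mentions a restriction to non-neurogenic dysphagia.

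**Step 5: size.** The quoted percentages are rates of dysphagia within each disease, not shares of the patients screened at this centre. The share lost would need the centre's case mix by cause, which the article does not give. No range can be derived without inventing that input.

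**The case against.** The strongest reply is that exclusion 5 is a loosely drafted comorbidity criterion. Malignancy is not a neurological disease, so the list is not tight enough to force the literal reading. Epilepsy fits the stated purpose of protecting participants from the device. Where the authors exclude by cause, as in exclusion 1, they say so, and exclusion 5 does not use that form. On this view 'other' was meant as other than the condition being treated.

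That intent is possible, but the text does not state it, and nothing in the inclusion criteria supplies the reference. If it was the intent, the criterion is misworded and still needs correcting, because a screener cannot tell which neurological patients to admit.

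A second reply is that the trial is not justified on stroke and Parkinson's disease alone. This stands. The objective names no disease, the background lists decreased muscle mass and reduced salivary secretion beside neurological disorders, and older adults have their own prevalence figure. A reader might infer that the whole target population has been excluded; the article does not support that.

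Other inferences also go too far:
- **Recruitment will fail.** No figure supports this prediction.
- **Paralysis removes both neurological groups.** It catches only some stroke patients.
- **The sample-size assumption comes from the wrong patients.** The sample-size section describes the source study only as one in dysphagia patients.
- **The cause of dysphagia will not be recorded at baseline.** A journal article commonly leaves its list of baseline variables to the full protocol.

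**Conclusion.** The conflict is real and lies in stated text. As written, exclusion 5 bars patients with stroke or Parkinson's disease, while the background and discussion justify the trial in substantial part, alongside older age and muscle weakness, on neurogenic and especially post-stroke dysphagia. The unrestricted wording of the objective and conclusion does not match the population that the literal criterion would admit.

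In size, two of the three groups cited for burden are excluded on the literal reading. That is a statement about the rationale, not an estimate of patients lost; the effect on reaching 78 participants cannot be calculated.

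The conclusion assumes only that stroke and Parkinson's disease count as neurological diseases and that screeners follow the criterion as printed. If screeners were told something else, the printed criterion does not describe the trial, and the need to correct it remains.

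**What to change.** Before recruitment starts, reconcile the eligibility criteria with the background, the objectives and the discussion by stating whether neurogenic dysphagia is eligible.

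- **If it is meant to be eligible:** reword exclusion 5 so that it does not catch the condition that caused the dysphagia, and check the word paralysis in exclusion 3 against the same intent.
- **If it is meant to be excluded,** for example as a participant precaution: say so in the objectives, and restrict the conclusions to non-neurogenic, non-structural dysphagia.

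Which option is clinically right is for the investigators; this review asks only that the sections agree.

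The cost is a one-line eligibility amendment with ethics approval and the registry update that the article's amendment procedure already provides for. The second option also needs short edits to the objectives and conclusions. The trial status section places the trial before recruitment, when the change is cheapest.

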### Who will take informed consent? {26a}

Based on the above criteria, patients with dysphagia who have been screened for eligibility to participate in this study will be invited to meet with the investigator to discuss the remaining questions and sign the informed consent form.

### Additional consent provisions for collection and use of participant data and biological specimens {26b}

If a patient withdraws consent, their data will be removed from the database and will not be used for analysis. In the case of study discontinuation, data may be retained if authorized by the patient. In such cases, primary and secondary outcomes will be assessed at the date of discontinuation.

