### Criteria for discontinuing or modifying allocated interventions {11b}

Neither the measurements nor the game manipulation produces any significant harmful side effects, as the game does not have graphic depictions of violence, and any of our measurements are not invasive. Therefore, we do not anticipate the need to modify the intervention during the study.

Patients can withdraw from the study at any time without adverse consequences for the patient. The investigator can also terminate a patient's participation in this study if the patient is uncooperative and/or does not attend the study visits. Patient data collected to date will be included in the analysis. If too much data is lost, the patient will be replaced by a new patient. The study will be terminated early in the event of serious adverse events, such as aspiration or vomiting.

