### Outcomes {12}

All assessments were completed by an experienced occupational therapist who was blind to the participants' group assignments. Assessments were conducted before the start of the intervention (pre-training), after 4 weeks of treatment (post-training), and at the 1-month follow-up (follow-up).

The primary outcome of this study was swallowing function, assessed using the Toronto Bedside Swallowing Screening Test (TOR-BSST) and the Functional Oral Intake Scale (FOIS). The Toronto Bedside Swallowing Screening Test (TOR‐BSST) is the best performing water swallow screening tool [21] with a sensitivity of 91.3%, a negative predictive value of 93.3% in the acute phase and 89.5% in the recovery phase [22]. TOR-BSST has shown to be more convenient and cheaper in bedside screening compared to the gold standard method of simultaneous videofluoroscopy (VFSS), which is an invasive assessment. Due to the limitations of the experimental site, we chose TOR-BSST as the assessment tool for dysphagia. FOIS consists of a 7-point scale, with level 1 indicating completely impaired oral intake and level 7 indicating complete oral intake regardless of food concentration or type [23].

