### Plans to promote participant retention and complete follow-up {18b}

During the recruitment process, participants will receive information about the study design and requirements. The researcher will explain to participants the benefits and implications of participating in the study and emphasize the importance of completing the study. Participants are permitted to withdraw from the study at any time during the study. Throughout the follow-up period, the researcher will monitor the participant's status at all times and contact the participant as necessary to complete the study. If participants withdraw from the study, efforts will be made to collect data on outcomes up to the time of withdrawal, with the participant's consent.

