## Statistical methods

### Statistical methods for primary and secondary outcomes {20a}

An intention-to-treat analysis will be performed, and the last available measurement will be used when data were lost due to dropout. Statistical analysis will be performed using SPSS 29.0. Statistical significance of all outcome variables will be established at *P* < 0.05.

All continuous data will be tested for normality, and nonparametric tests will be used for non-normally distributed data. Data conforming to normal distribution will be expressed as mean ± standard deviation (SD), and data with non-normal distribution will be expressed as median (interquartile range).

Comparisons of continuous data of two groups at the same time will be analyzed using independent samples t tests or rank sum tests, and comparisons of two groups of rates will be performed using chi-square test or Fisher exact test [31].

Comparison of continuous data trends over time between different groups at different times, if data normality is present, we will perform a series of repeated measures analysis of variance (ANOVA) for each outcome measure to assess differences between time (4 weeks and 1 month post) and between study groups, as well as interactions between time and study groups. For these analyses, the assumptions of sphericity and homogeneity of variances are tested using Mauchly and Levene tests [32]. If the assumption of sphericity is violated, the Huynh–Feldt correction is applied [32].

If the normality assumption is not met, the linear mixed model will be used for analysis, the comparative analysis at each time was performed using the nonparametric statistical Mann–Whitney U test and its own control two-way comparison using the nonparametric statistical Kruskal–Wallis rank sum test [33].

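### Patients who discontinue the study are assessed on the stop date, with no later week-4 or week-8 assessment provided, which undermines the stated intention-to-treat analysis

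*Protocol article*

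**What the plan says.** Outcomes {12} schedules assessment at baseline, after 4 weeks of treatment and at the 1-month follow-up (week 8), by a blinded assessor. Statistical methods {20a} promises: "An intention-to-treat analysis will be performed". It fills values lost to dropout with the last available measurement. Section {20c} repeats this and also names multiple imputation.

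Three sections say what happens when a patient leaves:

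- Consent provisions {26b}: "In the case of study discontinuation, data may be retained if authorized by the patient". It continues: "In such cases, primary and secondary outcomes will be assessed at the date of discontinuation".
- Retention {18b}: "If participants withdraw from the study, efforts will be made to collect data on outcomes up to the time of withdrawal, with the participant's consent".
- Discontinuation criteria {11b}: "The investigator can also terminate a patient's participation in this study if the patient is uncooperative and/or does not attend the study visits". Data gathered so far are analysed, and a patient with too much lost data may be replaced.

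Withdrawal of consent has its own rule in {26b}: "If a patient withdraws consent, their data will be removed from the database and will not be used for analysis". Those patients are outside this point.

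**The concern.** An intention-to-treat comparison at weeks 4 and 8 needs the outcome at those times, whether or not the patient kept training. Here the collection rule for patients who leave ends on the day they leave. A value taken in week 1, 2 or 3 is not a week-4 or week-8 FOIS or TOR-BSST result, and its timing differs from patient to patient. No analysis method can recover an outcome that could have been observed but was not collected. Carry-forward treats the early value as the later one, and imputation has to assume what the later one was.

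The loss could also be related to the allocated arm. The Background {6a} associates repetitive conventional training with low compliance, while the adherence section {11c} expects high compliance with the game. Both arms receive usual care, so some change after stopping is plausible. If leaving differs by arm, freezing outcomes at the exit date can create or hide a difference.

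**Working it through.** **1. What the sections provide together**

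| Situation | Outcome collection provided | Section |
|---|---|---|
| Completes the study | Baseline, week 4, week 8 | {12}, {18a} |
| Trains poorly, remains in the study | Not excluded from the three assessments; graded for adherence, with an added per-protocol analysis | {28-item adherence grading in {12}}, {18a}, {20c} |
| Discontinues the study, data kept | At the date of discontinuation | {26b} |
| Withdraws from the study | Up to withdrawal, with consent | {18b} |
| Ended by the investigator | Data to date analysed; replacement possible | {11b} |

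None of the last three rows has a later scheduled visit. In {11b} the two grounds for ending participation are joined by and/or, so lack of cooperation is enough by itself. A patient ended on that ground may still be willing to attend two bedside assessments.

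Stopping training while remaining available is foreseeable. Of 5 x 4 = 20 sessions, 17 are done without the researcher, and the adherence scale has a category below 50%, that is, fewer than 10 sessions. Yet no section defines when stopping training becomes leaving the study.

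**2. Which visits are lost**

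- Exit before week 4: both scheduled post-baseline outcomes.
- Exit between weeks 4 and 8: week 8 only.

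**3. The plan's own allowance**

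Sample size {14} gives 31 per group, raised for 20% dropout: 31 / 0.80 = 38.75, so 39 per group and 78 in total. The allowance is 78 - 62 = 16 patients. The 31 reproduces with a one-sided 5% t test (difference 1.00, pooled SD 1.329, power 90.06%). A two-sided test would need 39 before dropout; that is a separate matter.

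**4. Bias under carry-forward, unequal dropout (illustration)**

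Assumptions, none from the documents: a FOIS gain G by week 8 of 0.5 to 1.5 points, the same in both arms, linear in time and continuing off training; exit at week t = 1 to 3; dropout higher in controls by g = 0.10 to 0.20. There is no true difference between arms in this set-up, so any difference is spurious.

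Week 8: G x (8 - t)/8 x g

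- Low: 0.5 x 5/8 x 0.10 = 0.031
- Middle: 1.0 x 6/8 x 0.20 = 0.15
- High: 1.5 x 7/8 x 0.20 = 0.26

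Week 4: G x (4 - t)/8 x g

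- Low: 0.5 x 1/8 x 0.10 = 0.006
- Middle: 1.0 x 2/8 x 0.20 = 0.05
- High: 1.5 x 3/8 x 0.20 = 0.11

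Against the planned 1.0-point difference, the middle cases are 15% at week 8 and 5% at week 4. If the game arm loses more patients, g is negative and every sign reverses.

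**5. Equal dropout (illustration)**

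Assume that 20% leave early in each arm, the SD is unchanged, and the stop-date value holds a share f of the full 1.0-point effect. The observed difference is 1 - 0.20 + 0.20f. With 39 per arm and a two-sided 5% test:

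| f | Difference | Power |
|---|---|---|
| 0 | 0.80 | 74.7% |
| 0.5 | 0.90 | 84.0% |
| 1 | 1.00 | 90.7% |

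Here carry-forward works against the game.

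**The case against.** A reader might infer that any patient who stops training loses the week-4 and week-8 visits. The documents do not say so. The triggers are study discontinuation in {26b} and withdrawal from the study in {18b}. Section {18a} plans three assessments for each participant, Outcomes {12} grades poor adherence as a result to report, and {20c} handles non-adherence apart from dropout. Section {18b} also has the researcher contact participants so that they complete the study. On the natural reading, someone who merely trains too little is still due at all visits. This objection stands and limits the point to patients who leave, or are taken out of, the study. It does not remove the missing boundary between the two states.

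A reader might also infer that the effect of the game will be inflated. That direction needs more dropout among controls. The adverse event section {22} anticipates visual fatigue from the game, so the gap could go the other way. The calculations in step 4 also measure carry-forward, although {20c} names multiple imputation too. Both limits stand.

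It can further be said that the absence of a later visit is silence, and that an article leaves detail to the full protocol. This stands in part: {26b} does not say that assessment occurs only on the stop date. But the article does more than omit a detail. It states when leavers' outcomes are taken and, in {18b}, when collection ends.

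Lastly, patients who leave may refuse follow-up, and for them the proposed change gains nothing. That is true, and the recoverable share of the 16 allowed losses is unknown.

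**Conclusion.** The point holds for patients who discontinue the study, including those ended by the investigator. Their outcomes are set at the stop date, no later scheduled assessment is provided even for the willing, and an off-schedule value can enter the intention-to-treat analysis as week 4, week 8 or both. It would be too strong to say that such patients have no scheduled outcome at all, since those who leave after week 4 keep that visit.

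The finding rests on the text, not on a figure. The illustrated bias of 0.03 to 0.26 FOIS points at week 8 and 0.006 to 0.11 at week 4 depends on assumed recovery, exit time and dropout gap, and its direction is not determined by the documents. The protocol should be changed, because the remedy is specific and cheap; the documents do not show that the trial's result would be invalid without it.

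**What to change.** In {26b}, {11b} and {18b}:

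- Define stopping training and withdrawing from the study as separate events.
- State that any randomised patient in either arm who stops training, or whose training the investigator ends, is still invited to the scheduled blinded week-4 and week-8 assessments unless the patient declines further follow-up.
- Use those values in the intention-to-treat analysis.
- Keep the discontinuation-date assessment for patients who decline, label it off-schedule with its date, and do not enter it as the week-4 or week-8 value. Bring {20a} and {20c} into line with this.

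This is a change of protocol and consent wording, and the article describes the trial as not yet recruiting. It needs no change in sample size and no new procedure, because the visits are already in the schedule. The cost is some extra effort to bring patients back; some will decline, and their outcomes will remain missing.
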